[figure not shown]

## Summary of the study

**Full title of the project**

Physical inactivity and protein energy wasting play independent roles in muscle weakness and atrophy in maintenance haemodialysis patients.

**Background and rationale**

In chronic hemodialysis, uremic sarcopenia (with a prevalence of 20 to 50%), characterized by decreased mass and impaired muscle function is a significant mortality factor. The association of an increase in inflammation and oxidative stress, associated with kidney disease, defines the syndrome of Malnutrition, Inflammation and Atherogenesis (MIA syndrome). This syndrome is involved in the imbalance between anabolism and protein catabolism, which results in a decrease in the concentration of proteins necessary for muscle contraction. Thus muscle strength, dependent on muscle mass, could be limited by the MIA syndrome.

**Primary and secondary objectives**

- Main objective: To determine the contribution of the MIA syndrome in the reduction of muscle strength in chronic hemodialysis.

- Secondary objectives: In chronic hemodialysis determine:

The relationship between the maximal voluntary force (MVF) and muscle mass.

The relationship between MVF and lean mass.

The relationship between MVF and physical activity.

**Methods (study design, population, inclusion criteria, non inclusion, main and secondary evaluation criteria, number of topics to be included, statistical analysis ...)**

- Typology: Cross-sectional descriptive observational epidemiological study presenting minimal risks and constraints for the subject.

- Population (main eligibility criteria): chronic renal failure patients with chronic hemodialysis (> 3 months), aged between 18 and 90, with stable clinical status in the three months preceding inclusion.

- Criteria for judgment: The main criterion of judgment is the maximum voluntary force in Newton-meter.

**Procedure (number of visits, duration of inclusions, duration of follow-up, study schedule content of patient visits, brief description of the intervention):**

Two visits will be made.

The first visit (pre-inclusion) will verify the inclusion and non-inclusion criteria, inform the patient and obtain non-opposition to participate in the study.

The second visit will include:

- Measurement of MVF: Before the dialysis session

- Measurement of muscle mass by impedancemetry: after the dialysis session

- Collection of the biological parameters necessary for the estimation of the muscle mass and the MIA syndrome starting from the monthly report corresponding to the usual follow-up of the patient.

**Expected results and prospects**

Identifying the determinants of muscle strength in chronic hemodialysis will help to better understand the factors involved in the reduction of muscle strength. This will eventually allow to propose strategies based on the muscular retraining to prevent the appearance of a muscular deconditioning.

**Key words**

Key words: hemodialysis, muscle dysfunction, oxidative stress, inflammation.

# Background

4037/5000

Sarcopenia, defined as the association of loss of muscle mass and strength, is a geriatric process (1). The existence, in chronic hemodialysis, of a concomitant decrease in strength and muscle mass defines uremic sarcopenia, the prevalence of which is of the order of 20 to 50% (2). In this population, sarcopenia is a major prognostic marker of mortality (3).

The assessment of muscle mass is essential in hemodialysis because it is a reflection of the physical activity of patients and daily nutritional intake (4). Currently, two simple and quick bedside methods are used to evaluate the muscle mass of chronic hemodialysis patients (5,6). The first, the impedancemetry, measured by BCM (Body Composition Monitor, Fresenius Medical Care (6)), allows the measurement of lean mass (consisting of organs, skin, bones and muscles). The second, the creatinine index (CI) calculated from the parameters of hemodialysis and inter-dialytic production of creatinine, is a reflection of the metabolism of creatine and therefore of the muscle mass of hemodialysis patients (7). The limit of impedance measurement is the presence of an excess of inter-dialytic extracellular water. The measurement therefore needs to be standardized according to the periodicity of the dialysis sessions. The calculation of the creatinine index is modified by weekly changes in protein intake in patients (7). The isometric maximal voluntary force (MVF) is correlated with the surface of the muscle (r = 0.51) (8) in healthy subjects, and in some patients with chronic respiratory insufficiency (chronic obstructive pulmonary disease (9)). The measurement of muscle strength therefore appears as a new method of assessing muscle mass. Thus, in addition to allowing the functional assessment of the muscle (9), the isometric MVF of the quadriceps makes it possible to estimate the muscle mass of the patients outside certain neurological parameters (9). As a result, in chronic hemodialysis patients, MVF in combination with impedancemetry and the creatinine index would provide an accurate and rapid assessment of the patient's atrophy at the bedside.

The decrease in muscle mass in geriatrics results from an imbalance between anabolism and protein catabolism (1). Activation of protein catabolism is mediated by the ubiquitin-proteasome system (10). This pathway is activated by a reduction in the contractile activity of the muscle secondary to prolonged immobilization and by the reduction of physical activity of the patients (11). Anabolism is determined by physical activity and daily nutritional intake. In hemodialysis patients, in addition to decreased activity, undernutrition and immobilization, there are specific factors of muscle atrophy (11). Indeed, muscle atrophy may be the consequence of increased oxidative stress in this population (12) that results in activation of the ubiquitin-proteasome system (13). The syndrome of malnutrition, inflammation and atherogenesis (MIA syndrome), defined by an increase in inflammation and systemic oxidative stress (14), inducing an imbalance of the oxidation-reduction balance (15) could lead to a decrease the production of proteins necessary for muscle contraction (16). At the biological level, the markers of the MIA syndrome are the increase of the CRP and the decrease of the plasma albumin Thus the implication of the MIA in the imbalance between anabolism and protein catabolism, could explain its determining role in the appearance and the maintenance of muscle atrophy in chronic hemodialysis patients

WORKING HYPOTHESIS: In chronic hemodialysis, the MIA syndrome is a determining factor in the decrease in muscle mass estimated by the maximum voluntary force.

# Objectives of the study

## Primary objective

The primary objective of this study is to determine the contribution of MIA syndrome (increased CRP and decreased plasma albumin) in the decrease of MVF in chronic hemodialysis patients.

## Secondary objectives

In patients on chronic hemodialysis (HDC):

- The relationship between the MVF and the muscle mass appreciated by the creatinine index.

- The relationship between MVF and lean mass measured by impedance measurement.

- The correlation between MVF and physical activity estimated by the Voorrips score.

# Methodology

## Experimental design

### Type of study

Multidisciplinary cross-sectional descriptive observational epidemiological study presenting minimal risks or constraints for the subject.

## Subject selection

### Population

Patients with chronic renal failure at the end stage, chronic hemodialysis for at least 3 months.

### Inclusion criteria

| Age > à 18 years et < 90 years |
| --- |
| Chronic end-stage renal failure patient (GFR <15ml / min), with chronic dialysis hemodialysis treatment for at least 3 months. |
| Cardiovascular assessment less than two years old |
| Stable clinical status: In the three months prior to inclusion  -Absence of infection  -Absence of acute decompensation, chronic pathology (heart failure, respiratory failure, oedemato-ascitic decompensation).  -Absence of stroke. |
| Locomotive and neurological states of the lower limbs for the realization of the proposed functional tests. |
| Absence of congenital or genetic neurodegenerative muscular pathology |
| Collection of non-opposition to participation in the protocol |
| Obligation of affiliation or beneficiary of a social security scheme. |

### Exclusion criteria

| Major subject protected by law or unable to express his opposition to participation in the study according to Article L 1121-8 of the Public Health Code |
| --- |
| Vulnerable person according to article L.1121-6 of the Public Health Code |
| Subject not affiliated to a social security scheme, or not a beneficiary of such a schem |
| Chronic end-stage renal failure without adjunctive therapy |
| History of renal transplantation, in progress or having been resumed in hemodialysis in the 365 days preceding the day of inclusion. |
| Subject deprived of liberty by judicial or administrative decision |
| Cardiovascular contraindication to physical activity |
| Pregnant or breastfeeding women according to Article L.1121-5 of the Public Health Code |

## Description of intervention (s)

**Assessment of strength and muscle mass. :**

The measurement of the maximum voluntary force will be performed before the hemodialysis session

The measurement of muscle mass will be performed after the hemodialysis session

**Clinical data:**

From the clinical and biological parameters of the patient in his medical file: evaluation of his antecedents, comorbidities and systemic parameters of the MIA syndrome.

## Judgment criteria

### Main judgment criteria

In HDC patients, the multivariate analysis of the determinants of MVF (in Newton per meter): Muscle mass by impedancemetry and the Creatinine Index; the concentration of CRP and plasma albumin (MIA syndrome); physical activity by the Voorrips score.

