## Statistics:

### Expected number of people to be included in the study

Considering a linear multivariate model with 5 covariates (albumin - CRP - Voorrips score - LBM - creatinine index), a risk of the first species of 5%, a desired power of 90% and a force of the effect of 0, As proposed by Cohen (Cohen Behavioral Sciences 1988) it will be necessary to include 110 patients. The calculation was carried out on the software R 3.1.1 (R Coreteam, Vienna, Austria) package pwr.

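### The only multivariable model for the primary objective holds muscle mass fixed, so its CRP and albumin coefficients omit the part of the MIA effect that passes through muscle loss

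*Protocol*

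**What the plan says.** The Protocol's Primary objective is to "determine the contribution of MIA syndrome (increased CRP and decreased plasma albumin) in the decrease of MVF in chronic hemodialysis patients". It does not say whether this contribution is overall or at a given muscle mass.

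The mechanism is described in two places. The Summary (Background and rationale) says: "Thus muscle strength, dependent on muscle mass, could be limited by the MIA syndrome". The Background section says that the involvement of MIA in the balance of protein synthesis and breakdown "could explain its determining role in the appearance and the maintenance of muscle atrophy in chronic hemodialysis patients", and ends with the working hypothesis: "In chronic hemodialysis, the MIA syndrome is a determining factor in the decrease in muscle mass estimated by the maximum voluntary force".

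The covariates are fixed twice. Main judgment criteria lists them as "Muscle mass by impedancemetry and the Creatinine Index; the concentration of CRP and plasma albumin (MIA syndrome); physical activity by the Voorrips score". The sample size section (Expected number of people to be included in the study) is built on a "linear multivariate model with 5 covariates (albumin - CRP - Voorrips score - LBM - creatinine index"), the same five variables. The statistical methods section adds only that the multivariate analysis is a multiple linear regression. No model of MVF on CRP and albumin without the two mass measures is stated, and no staged entry or mediation analysis.

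Outside the regression, Secondary endpoints lists a Pearson correlation of albumin with MVF but none for CRP. The statistical methods section also promises univariate correlations between the judgment criteria, which could be read to cover CRP.

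**The concern.** Set out as a path, the Protocol's reasoning is MIA → protein loss → lower muscle mass → lower MVF. Lean mass by impedance and the creatinine index are both presented as measures of that intermediate step. Regressing MVF on CRP and albumin with both held fixed compares patients who differ in MIA markers but have the same muscle mass. That comparison leaves out the route the working hypothesis names.

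The creatinine index adds a further overlap. The section on parameters collected says that it reflects nutritional status as well as muscle mass, so adjusting for it also takes out some of the malnutrition component of MIA.

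What is at stake is interpretation. A small or non-significant CRP or albumin coefficient could be reported as MIA making little contribution to weakness, when the data might show that it contributes through atrophy, as the investigators propose.

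**Working it through.** **The plan's own figure.** The sample size section gives 110 patients for five covariates, 5% alpha and 90% power. The effect size is cut off in the available text, so 110 cannot be reproduced from the stated inputs. The calculation describes a five-covariate model and singles out no MIA terms. N = 110 is taken as given below, and the structural point does not depend on it.

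**Structure.** Use standardised variables: X an MIA score (oriented so that the effects are positive), M muscle mass, Y MVF.

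- M = aX + error; Y = dX + bM + error
- Total effect T = d + ab; coefficient of X with M in the model = d
- Share of T removed by adjustment = ab / T

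**Inputs.** b = 0.51 is the correlation of muscle surface with MVF that the Background section cites for healthy subjects. It is borrowed here as the mass-to-strength path, which is an assumption for dialysis patients. The Protocol gives no value for a, d or T, so ranges are shown.

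**Share removed.**

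- d = 0: 100%, whatever the value of a.
- d = 0.1, a = 0.2: ab = 0.102, share = 0.102/0.202 ≈ 50%.
- d = 0.1, a = 0.5: ab = 0.255, share = 0.255/0.355 ≈ 72%.

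**Power for a single MIA score, N = 110, two-sided 5%.**

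- Without M: f² = T²/(1 − T²), F test on 1 and 108 df.
- With M: r(M,Y) = b + da; R² = dT + b·r(M,Y); ΔR² = R² − r(M,Y)²; f² = ΔR²/(1 − R²), F test on 1 and 107 df.
- Noncentrality in both cases: 110·f².

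Example with T = 0.3, half mediated: a = 0.15/0.51 = 0.294 and d = 0.15. Then r(M,Y) = 0.51 + 0.15 × 0.294 = 0.554, R² = 0.15 × 0.3 + 0.51 × 0.554 = 0.328, ΔR² = 0.021, f² = 0.031 and power is 0.44. Without M, f² = 0.09/0.91 = 0.099 and power is 0.90.

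| Total effect T | Power without mass | With mass, 0% mediated | With mass, 50% | With mass, 75% | With mass, 100% |
|---|---|---|---|---|---|
| 0.2 | 0.56 | 0.70 | 0.23 | 0.09 | 0.05 |
| 0.3 | 0.90 | 0.97 | 0.44 | 0.13 | 0.05 |
| 0.4 | >0.99 | >0.99 | 0.68 | 0.18 | 0.05 |

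In the last column the coefficient is zero, so the rejection rate is alpha.

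**Simulation closer to the planned model.** N = 110; albumin and CRP correlated −0.35; two mass measures, each with reliability 0.8; path from each marker to mass 0.25–0.30; b = 0.51; 2-df test of albumin and CRP. All of these settings except N and b are assumed.

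- No direct effect: about 5–6% with the mass measures, about 50–65% without.
- Direct effect 0.1 on each marker: about 48% with, about 96–99% without.
- Direct effect 0.2 on each marker: about 98% even with the mass measures.

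**The case against.** The strongest reply is that the five-covariate model answers a legitimate question. The objective says only contribution, Main judgment criteria speaks of determinants of MVF, and the full title refers to independent roles. The Summary and Background also describe a shortage of the proteins needed for contraction, which could weaken muscle at unchanged mass. An MIA coefficient adjusted for mass would keep that effect. This stands. A reader might infer that the model excludes everything the study set out to find, or that the result will probably be falsely negative. The Protocol does not support either inference, because both need nearly complete mediation, which it nowhere asserts. The table and the 0.2 scenario show the adjusted model performing well when the effect is largely direct. The independence in the title is, besides, between inactivity and wasting, with atrophy named as an outcome beside weakness.

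Second, univariate correlations of albumin, and arguably CRP, with MVF would be reported alongside. This softens the problem but does not cure it. They are unadjusted for age, sex and body size, and they are not the primary analysis.

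Third, a statistical analysis plan may exist and could add staged models. But the Protocol itself fixes the covariate set in both the primary criterion and the sample size section, so this choice is not one it leaves open.

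Fourth, dropping the mass measures brings its own risk. Lean mass is the only term tied directly to body size, MVF is a torque, and the creatinine index carries age and sex. Physical activity may also lie downstream of MIA rather than confound it. Both points are fair and shape the fix.

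**Conclusion.** The point holds in a limited form. The single multivariable model stated for the primary objective estimates the MIA association beyond muscle mass and omits the mass-mediated part, which is the part the working hypothesis names. That follows from the Protocol's own text without any assumed number.

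The size of the loss does rest on assumptions: b = 0.51 from healthy subjects, and unknown MIA-to-mass and direct paths. Under full mediation the coefficients would be near zero with the hypothesis true, with power of about 5% against about 50–65% without the mass measures. With a modest direct effect the loss is partial (about 48% against 96–99%), and with a larger one it is negligible.

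The design is cross-sectional, so mediation is the Protocol's hypothesis and the study cannot establish it. Every patient's data remain usable and both models can be fitted, so this should be fixed but does not invalidate the study.

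**What to change.** In Main judgment criteria, and correspondingly in the sample size section:

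- State which MIA contribution is meant, overall or beyond muscle mass.
- For the overall contribution, pre-specify MVF on albumin, CRP, age, sex and height, without lean mass and creatinine index. Height stands in for body size without bringing muscle mass back in, as weight would. Fit it with and without the Voorrips score, since activity may itself be a consequence of MIA.
- Keep the five-covariate model and label it as the MIA association beyond muscle mass.
- Report the two side by side, and state in advance that a null MIA result in the mass-adjusted model will not be read as no contribution of MIA.

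Age and sex already enter the creatinine index. Height is named with age, weight and sex in the Expected Results section as a basis for MVF values, so it only needs confirming that it is on the case report form. The cost is one extra regression (fitted with and without Voorrips), two estimates to explain, and causal wording kept within what a cross-sectional study allows.

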### Secondary endpoints

In patients with HDC:

- the linear correlation (Pearson) between the creatinine index and the MVF.

- the linear correlation (Pearson) between the lean mass estimated by impedancemetry and the MVF.

- the linear correlation (Pearson) between the Voorrips score and the MVF.

- linear correlation (Pearson) between plasma albumin concentration and MVF

- linear correlation (Pearson) between hemoglobin concentration and MVF

## Parameters collected and method of collection

**Clinical parameters:**

Physical Activity Questionnaires:

The evaluation of the different types of activities (domestic, leisure, sports) will be made using the questionnaire of Baecke modified by Voorrips, which informs on the physical activity carried out in the previous year. This questionnaire has been used in several previous studies by INSERM Unit U1046.

Screening for comorbidities:

Charlson score, already validated in nephrology in chronic hemodialysis patients.

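### The Charlson score is collected but has no inferential role, so the estimated contribution of CRP and albumin to MVF may be confounded by chronic comorbidity, to an extent the protocol does not allow one to size

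*Protocol*

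**What the plan says.** Under Parameters collected and method of collection, the protocol lists for comorbidity screening the "Charlson score, already validated in nephrology in chronic hemodialysis patients". The Clinical data paragraph under Description of intervention(s) draws from the medical file an "evaluation of his antecedents, comorbidities and systemic parameters of the MIA syndrome".

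The primary objective is to "determine the contribution of MIA syndrome (increased CRP and decreased plasma albumin) in the decrease of MVF in chronic hemodialysis patients".

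The primary model is set out twice with the same terms:
- Main judgment criteria gives the determinants of MVF as "Muscle mass by impedancemetry and the Creatinine Index; the concentration of CRP and plasma albumin (MIA syndrome); physical activity by the Voorrips score".
- The sample-size section begins "Considering a linear multivariate model with 5 covariates (albumin - CRP - Voorrips score - LBM - creatinine index".

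Charlson is in neither list. It is not among the five Pearson correlations under Secondary endpoints. The planned statistical methods name multiple linear regression but no adjustment variables. The only use open to the score is the general descriptive analysis.

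**The concern.** CRP and albumin are non-specific markers. Chronic disease burden could raise CRP, lower albumin and weaken the quadriceps at the same time. If it does, a regression without a measure of that burden credits part of its effect to CRP and albumin, and the answer to the primary objective is distorted. The study's full title speaks of independent roles, and a claim of independence depends on which common causes the model holds.

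Eligibility does not remove the issue. The inclusion criteria require three months without infection, acute decompensation or stroke. That limits acute illness but leaves chronic burden in place.

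The SAP is not at hand, and adjustment detail is often left to it. Here, however, the protocol itself fixes the five terms in two sections, so an SAP that follows it would leave Charlson out of the primary model.

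**Working it through.** **1. The plan's own figure.** The stated size is 110 for five covariates, with "a risk of the first species of 5"% and "a desired power of 90"%. The effect size is not legible after the decimal mark, so 110 cannot be rebuilt from stated inputs. For the overall F test, λ = f²(u + v + 1), with u covariates and N = u + v + 1. Assumed values give:
- f² = 0.10: N = 171
- f² = 0.15: v = 109.5, N = 116
- f² = 0.16: N = 109
- f² = 0.20: N = 89

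Exactly 110 needs f² = 0.158. I use N = 110 below because it is both the stated size and the stated recruitment potential.

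**2. What omission could do to the CRP test.** The protocol gives none of the correlations needed, so all those used here are assumptions. Setting: n = 110, no true CRP effect, five-term model, two-sided t test at 5%, 6,000 simulated studies per scenario. If the other four covariates are independent of Charlson, the spurious CRP-MVF correlation is the product of the two links, for example 0.4 × (-0.3) = -0.12.

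Hand check of that case: residual df = 110 - 6 = 104. The shift is 0.12 × √104 / √(1 - 0.0144) ≈ 1.23 standard errors against a critical value of 1.98. The gap of 0.75 leaves a tail of about 23%.

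The second set of rows assumes instead that Charlson correlates -0.3 with each of lean mass, creatinine index and Voorrips score, and varies the share of the Charlson-MVF link that runs through them.

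| Charlson-CRP / Charlson-MVF | 0.2 / -0.2 | 0.2 / -0.3 | 0.3 / -0.3 | 0.4 / -0.3 |
|---|---|---|---|---|
| Spurious correlation, other covariates independent | -0.04 | -0.06 | -0.09 | -0.12 |
| False positives, other covariates independent | 6.9% | 9.1% | 15.2% | 23.1% |
| Correlated -0.3, none of the link through them | 6.4% | 7.9% | 11.6% | 15.6% |
| Half through them | 5.3% | 6.0% | 6.1% | 8.9% |
| Three quarters through them | 4.6% | 5.2% | 5.4% | 5.6% |
| All through them | about 5% | about 5% | about 5% | about 5% |

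With Charlson in the model the rate is about 5% throughout. Simulation error near 5% is √(0.05 × 0.95 / 6000) ≈ 0.3 percentage points.

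**3. The joint test.** The protocol defines MIA by CRP and albumin together, so the 2-df test is closer to the objective. Assume Charlson correlates 0.2 to 0.4 in absolute value with all five covariates and has a direct effect on MVF of 0.2 to 0.5 residual SD. The test then rejects in about 7% to 30% of null studies without Charlson and in about 4% to 5% with it. If either link is zero, rejection stays near 5%.

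**4. Cost in power at N = 110.**
- Overall F test, f² = 0.15: 88.2% with five covariates, 85.7% with six.
- Joint CRP + albumin test, f² = 0.15: 95.7% with either.
- Joint CRP + albumin test, f² = 0.10: 84.2% with either.

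**The case against.** The strongest reply has four parts.

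*No link is documented.* Nothing in the protocol ties Charlson to CRP, albumin or MVF. A reader might infer that the MIA estimate is confounded, or is biased away from zero. The document supports neither statement: the existence, direction and size of any bias all depend on correlations it does not give. This part stands, and the point is limited to possible confounding of unknown size.

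*The model may already block much of the path.* Lean mass, creatinine index and physical activity are natural routes from comorbidity to weak quadriceps, and the Background itself names reduced activity and immobilisation as causes of atrophy. A reader might take 15% to 23% as the expected error rate. Those figures need the other covariates to be independent of Charlson, and the rate falls towards 5% as they carry more of the effect. This part also stands.

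*Charlson may not be a clean confounder.* The exposure is a syndrome of malnutrition, inflammation and atherogenesis. Some cardiovascular comorbidity may be part of it or a consequence of it, and adjustment could remove some of the effect sought. A reader might conclude that the five-term model is wrong and should be replaced. The documents do not support that, but the argument does not count against reporting both models.

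*The score may be only descriptive, with adjustment left to the SAP.* Screening for comorbidities is the stated purpose, and the sample-size model is a premise rather than a list of exclusions. It is fair that nothing here is a contradiction and that a descriptive use is open. It does not explain why the criterion section, which names the terms of the primary analysis, gives the only comorbidity score no part in it.

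**Conclusion.** The point holds in a limited form. The protocol collects Charlson, fixes the primary model twice without it and assigns it no inferential use, while its primary objective asks for the contribution of markers that comorbidity could plausibly influence. The estimate may be confounded; how much cannot be derived from the document.

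The range of about 5% to 23% for the CRP false-positive rate illustrates sensitivity to assumptions and does not predict this study's error rate. Bias needs both a link from comorbidity to the markers and a link to strength beyond the other model terms. This is a cheap improvement to the plan, not an error that invalidates the primary analysis.

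**What to change.** Keep the five-term model. In Main judgment criteria and the statistical methods, prespecify a second multiple regression that adds the Charlson score, leaving out any age points if age is also entered. Report the CRP and albumin estimates with confidence intervals from both models, ideally with their joint 2-df test. Limit any statement of an independent MIA contribution to what holds in both.

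The cost is one degree of freedom and one extra model, with no new data and almost no loss of power for the joint MIA test. The adjusted estimate may be conservative if some cardiovascular comorbidity is part or a consequence of MIA, which is the reason to show both.

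Charlson alone does not deal with age and sex. They have no terms of their own and enter only through the creatinine index, although Expected Results and Outlook anticipates MVF values by age, weight, height and sex.
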